# HOme-based self-sampling for cervical cancer prevention education among women living with HIV in Ghana (HOPE-inG): study protocol for a cluster-randomized type 2 hybrid effectiveness implementation trial

**DOI:** 10.1186/s12889-026-26505-2

**Published:** 2026-03-27

**Keywords:** Women, HIV, HPV, 3R model, Cervical cancer, Ghana, HIV infections, Health education

## Abstract

**Background:**

Women living with HIV (WLWH) are six times more likely to develop cervical cancer (CC) than women without HIV, underscoring the urgent need for early and frequent screening. In Ghana, however, screening uptake among WLWH remains critically low and no national screening program exists. The HOPE (HOme-based self-sampling Prevention Education) toolkit has proven effective in increasing screening uptake. HOPE-inG (HOPE 2.0 in Ghana) aims to adapt the HOPE toolkits and develop implementation support strategies (ISS) to enhance the uptake and sustainment of cervical screening within HIV care services.

**Methods:**

This study will be conducted in four HIV clinics in Ghana’s Central Region using a three-phase design.

Preparation Phase (Year 1): Use mixed methods, including nominal group techniques with 40–60 stakeholders (WLWH, healthcare providers, policymakers), to prioritize ISS and refine HOPE into HOPE 2.0 or HOPE-inG.

Implementation Phase (Years 2–3): Conduct a hybrid type 2 cluster-randomized controlled trial, comparing HOPE 2.0 + ISS (intervention group) versus HOPE 2.0 alone (control group). A total of 1,152 WLWH and 80 health providers will be enrolled.

Sustainment Phase (Years 3–5): Evaluate the long-term sustainment of HOPE 2.0 and ISS using quantitative and qualitative methods.

Primary outcomes include patient-level screening and treatment uptake (effectiveness) and provider-level implementation metrics (adoption, cost, fidelity, penetration and sustainability). Data sources include surveys, interviews, electronic tracking and fidelity checklists at multiple organizational levels. Cost analyses will employ micro-costing methods, and fidelity will be monitored through structured observations and log sheets.

**Discussion:**

HOPE-inG is designed to develop scalable, sustainable strategies for improving cervical screening and care among WLWH in Ghana. By embedding evidence-based screening tools within HIV care services and supporting providers with targeted ISS, this study seeks to bridge critical gaps in cervical cancer prevention. Findings will provide evidence to inform national policy and guide the broader implementation of patient-driven and community-based screening programs in other low-resource settings, ultimately improving health outcomes and reducing disparities for WLWH.

**Trial registration:**

ClinicalTrials.gov NCT06800664. Registered on 29 January 2025.

**Supplementary Information:**

The online version contains supplementary material available at 10.1186/s12889-026-26505-2.

## Background

Women living with HIV (WLWH) have a six-fold higher risk of developing cervical cancer (CC) than women without HIV [1]. The World Health Organization (WHO) recommends nucleic acid-based human papillomavirus (HPV) testing for cervical screening (CS) among WLWH beginning at age 25 years, and every 3 to 5 years thereafter [2]. Early detection and prompt treatment of precancerous lesions of the cervix are crucial to preventing CC in this high-risk group CC [3–5]. However, women in low and middle-income countries (LMICs) face significant challenges in accessing cervical screening and treatment services.

Ghana, with an HIV prevalence of 1.7% in the general population, has a feminized epidemic: approximately 64% of the estimated 330,000 people living with HIV are women, aged 15 years and above [6–9]. However, Ghana lacks a national cervical screening program [10–13] and CC prevention programs are not commonly promoted. Screening rates are extremely low, with only 2.7% of eligible women ever screened [14]. Among those who test positive for high-risk HPV, many are lost to follow-up [13, 15, 16]. There is no evidence that WLWH are screened or treated at higher rates than women without HIV. These gaps are particularly consequential for the estimated 69,000 Ghanaian WLWH, who remain at increased risk [17]. In Ghana and other low- and middle-income countries, barriers to attaining the WHO goal of at least 70% cervical screening rates and subsequent treatment [18] include limited healthcare funding, inequitable distribution of services, and limited capacity of healthcare workers [12, 16, 19, 20]. Other barriers include misconceptions, cultural beliefs, and societal stigmatization, fear of pain, prohibitive costs, privacy concerns, and low prioritization of cancer screening [21, 22].

To address some of these challenges, our research team developed and tested a HOme-based self-sampling cervical cancer Prevention Education (HOPE) toolkit [23]. The HOPE toolkit consisted of HPV self-sampling, the 3R (Reframing, Reprioritizing, and Reforming) communication model [23–26] and patient navigator support. The current study is an extension of the HOPE initiative to promote cervical screening among women WLWH in Ghana (hereafter referred to as HOPE-inG or HOPE 2.0). HOPE-inG retains the three core components of the original HOPE intervention and introduces a fourth component: implementation support strategies (ISS), which we define as implementation strategies most relevant to implementation support, which is concerned with moving (implementation) research into (implementation) practice. ISS facilitate health system adoption and sustainment and function most directly within the implementation setting and at the interface between implementation and policymaking entities.

### Study aims

Although HOPE components have been rigorously tested and found impactful in our Ghanaian study setting, the absence of implementation strategies and a structured implementation plan has limited their translation into routine clinical practice. An implementation science approach guides the development of implementation strategies for adopting and translating this next phase of HOPE 2.0 into routine health practice in Ghana. Our study aims are as follows:To develop a culturally appropriate, evidence-based implementation plan and provider training materials to support the effective delivery of the HOPE 2.0 intervention within Ghana’s health system.To evaluate the effectiveness of the HOPE 2.0 intervention and its implementation strategy through a hybrid type 2 implementation-effectiveness trial.To assess the impact of the implementation plan on the sustainment of the HOPE intervention at participating HIV clinics.

## Methods

This HOPE-inG study is a two-arm, cluster-randomized type 2 hybrid effectiveness implementation trial.

### The HOPE intervention

The evidence-based intervention (EBI) for our study is HOPE’s three-component combination intervention: a cervical screening self-sampling kit, the 3R communication model, and patient navigator support.

#### Evidence-based HPV self-sampling

HPV self-sampling (HPVSS) is a feasible and effective cervical screening strategy [27–30]. It involves women collecting their own vaginal samples, which are then sent to health facilities or laboratories for analysis to detect HPV strains. Compared with clinician-collected samples, HPVSS can help overcome both structural and individual-level barriers to cervical screening and thus increase participation [31]. Meta-analyses indicate that HPVSS is comparable in sensitivity to clinician-collected PCR samples and demonstrates a high level of agreement with clinician-led detection methods [27–30]. Our previous Ghana-based studies confirmed HPVSS to be culturally acceptable [32–36] and effective in detecting precancerous lesions among WLWH in Ghana [35].

The WHO recommends HPVSS for use in LMICs [35, 37, 38]. However, despite its potential to increase screening uptake, its utilization is constrained by factors like insufficient awareness, perceived difficulty with self-sampling, and fear of positive results [39–41]. Effective communication is therefore needed to increase public engagement on HPVSS. To address this, we integrated the 3R communication model into HOPE [42, 43].

#### Evidence-based 3R communication model

The dimensions of the 3R communication model are reframing, reprioritizing, and reforming. Reframing is derived from health communication strategies [34, 35] that contrast the consequences of not screening and delayed treatment of precancerous lesions of the cervix (loss-framed appeals) with the benefits of early detection and treatment (gain-framed appeals). Reprioritizing prompts individuals to consider the relatively low cost of screening and treating precancerous lesions against the significantly higher cost of cancer treatment and possible loss of life. Reforming involves correcting misconceptions about self-sampling to promote positive attitudes toward screening and treatment. In Ghana, application of the 3R model within the HOPE toolkit significantly increased screening uptake and treatment compliance, achieving100% rates in the intervention group [36, 37].

#### Evidence-based patient navigator support

Patient navigators, trained lay or volunteer health workers, play a vital role in improving equitable access to, and sustained use of HPVSS [37]. In Ghana, they routinely deliver health education and community-based services for various conditions, including breast cancer and HIV [44]. Within the HOPE intervention, patient navigators motivated WLWH, facilitated questionnaire completion, addressed participant questions, and ensured timely distribution and return of HPVSS kits. These activities enhanced service uptake, improved screening rates, and reduced diagnostic delays, consistent with findings from other LMICs [23, 45, 46].

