### Site selection

The proposed research will be conducted in the Central Region, home to approximately 2.8 million people [54] and has the fifth-highest HIV burden among Ghana’s 16 regions [55]. We will leverage established partnerships with HIV clinics in the Central Region and with the National AIDS/STI Control Program (NACP) to select secondary-level facilities with similar infrastructure. In the Central Region, 85 antiretroviral therapy (ART) clinics operate across 22 districts. The selection criteria included: a clinic that is the largest district-level hub site, has highly accessible spokes, and has enrolled at least 400 WLWH on ART. The largest hub sites that have already established access to cervical cancer screening and treatment services at a tertiary referral facility were excluded. A master list of study-eligible women was developed through the existing HIV E-tracker electronic medical record system. Ultimately, four study sites were selected for randomization for the intervention arm (two sites: Our Lady of Grace Hospital, Breman Asikuma and Saltpond Municipal Hospital, Mfantseman) and the control arm (two sites: Saint Francis Xavier Hospital, Assin Fosu and Swedru Government Hospital, Agona West). 

The combined workforce across the selected sites includes approximately 500 staff and a total bed capacity of over 700. For project implementation, we will engage existing personnel, including health facility administrators, clinicians (doctors, nurses, midwives), and support staff (including patient navigators), collectively referred to as “healthcare providers”.

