### Implementation phase

Assess the effectiveness of the HOPE 2.0 intervention and the success of the implementation plan in a hybrid type 2 trial.

*Hypothesis: Cervical screening uptake by HPVSS will be significantly higher among WLWH in the intervention vs. the control group, and implementation outcomes scores among intervention group providers will be significantly higher than those of control group providers.*

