### Inclusion and exclusion criteria and recruitment

#### Inclusion criteria

General eligibility criteria are living and/or working in the Central Region and ≥ 18 years old.Specific eligibility criteria for providers are to possess healthcare training and/or qualifications (i.e., patient navigators, physicians, nurses) and work at the HIV clinic; for clinic managers, health facility management in administrative leadership, and oversee HIV clinic operations.Study eligibility criteria for women in the trial include women who are living with HIV (regardless of pregnancy status), between 25 and 65 years old (age consistent with WHO cervical screening guidelines [2]); have never had cervical screening (Pap smear or HPV test), or have not had cervical screening in the last five years.Eligible community members include individuals (with and without HIV and/or cervical cancer) living in the study communities and/or family members of WLWH.Eligible policymakers include personnel from the National AIDS/STI Control Program, Ministry of Health, and Ghana Health Service.

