#### Recruitment

*Doctors, nurses, patient navigators, and clinic managers:* We will meet with Medical Directors of the selected health facilities to discuss the study and the recruitment of providers. We will recruit providers by email, phone, and face-to-face contact.*WLWH* will be recruited using E-tracker electronic records. Participating providers at each site will identify eligible women from their site-level sampling frame (400–600 per site for a total pool of ~ 3,900 WLWH) and contact them by phone to solicit participation. Verbal informed consent will be sought in English/applicable local language by research coordinators prior to trial initiation. Participant recruitment is ongoing and will be completed by March 2028.*Community members* will be recruited from study communities via community gatekeepers.Ghana Health Service and the Ministry of Health will facilitate the recruitment of government officials through written and verbal invitations and snowball recruitment.

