#### Control arm

Providers and clinic managers at control sites will receive baseline training on study implementation, but will not receive any ISS or implementation plan training (Table 2). They will, however, be required to follow Steps 2, 3, and 4 described in the intervention arm described above, except for patient navigator support.

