### Outcomes measures

The primary outcomes of interest in this type 2 hybrid trial are 1) the effectiveness of the HOPE 2.0 intervention in increasing uptake of cervical screening among WLWH, and 2) the adoption of HOPE 2.0 intervention at the facility level. Other outcomes, including cost, fidelity, penetration, and sustainability, will be assessed as secondary outcomes. Additionally, Proctor et al.’s [61] client (i.e., WLWH) health outcomes will also be assessed (Fig. 2).*Cervical screening uptake* is defined as the proportion of WLWH in each study arm that successfully complete the cervical screening process. In the intervention arm, completing the process requires the WLWH to present to the clinic, collect a self-test kit, collect a cervical sample, and submit the sample to the clinic for testing. In the control arm, completing the process requires the WLWH to present to the clinic and receive a pap smear/cervical sample collection from a provider. WLWH in either study arm who do not complete the entire process will not be considered as completing uptake. Uptake assessment will therefore be determined as proportion of WLWH with complete screening out of all women enrolled in each study arm.*Program Adoption* is defined as the decision of healthcare workers (i.e., providers and management) and patients (described as patient uptake) to commit to and use HOPE 2.0 and ISS adoption. Adoption will be measured at provider, management, and patient levels using a variety of data logs, surveys, and interviews.At the management level, we will assess (i) the number of ISS training sessions attended and (ii) the degree to which ISS components are used to support providers.At the provider level, we will assess (i) the number of ISS training sessions attended, (ii) the degree to which ISS components are used, and (iii) the number of implementation plan steps followed. Additionally, we will assess providers’ (i) implementation experience (i.e., resource availability, managerial support, and technical issues confronted); and (ii) operational experience (i.e., workload increase or decrease, flow of health facility communication, and any skills needed).*Implementation Cost* is defined as the total expenses (facility/provider and patient) for implementing HOPE 2.0. Cost will be assessed at the health facility level in both study arms. We will use a micro-costing approach to estimate the economic costs associated with each study arm. The direct measure method of micro-costing involves tracking resources used and enumerating unit costs for each resource to precisely estimate cumulative costs associated with each study arm [62]. Implementation cost will be measured at the health facility level and patient level, utilizing a variety of cost-tracking databases throughout the study period to itemize, quantify, and value resources.At the health facility level, a cost-tracking database will be used throughout the study period to itemize, quantify, and value resources. Costs at the facility level include (i) number of hours staff spent on HOPE 2.0 training; (ii) sampling materials, including kits and laboratory testing costs; (iii) recruitment (i.e., time spent identifying and contacting eligible women, advertising materials, participant incentives); (iv) HOPE 2.0 delivery (with and without ISS); and (v) treatment and biopsies.Cost to the patient will include tracking of participant out-of-pocket costs (e.g., transportation, childcare, phone data, time spent on HOPE 2.0 procedures). French et al.’s outpatient cost survey [63] (5 items) will be adapted to measure patient-level costs.Note: Time effort will be estimated using the hourly wages of WLWH and healthcare workers.*Fidelity* is the degree to which HOPE 2.0 and its ISS are implemented as planned.At the provider level, utilizing surveys, log sheets, and interviews, we will assess (i) the degree of adherence to HOPE 2.0/ISS protocols (Intervention) and HOPE 2.0 (Control) during implementation, (ii) the dose of the program delivered, and (iii) the quality of program delivery.At the management level, we will assess (i) adherence to ISS protocol (Intervention only) and (ii) overall management support for providers (both arms).We will utilize log sheets and interviews, as well as observations, and the Process Evaluation Checklist (PEC) [64] throughout to track the fidelity of implementation and overall project progress.*Program Penetration* for this proposal is the integration of HOPE 2.0/ISS within the HIV subsystem of study facility settings [61]. We will assess penetration outcomes at provider and management levels by determining the proportion of personnel who actually deliver on a HOPE 2.0 program task/role, out of the number trained or expected to deliver on that task/role.At the management level, we will utilize log sheets and interviews to measure the expected tasks or roles to be evaluated, which will be (i) the provision of technical support and (ii) facilitating a conducive HOPE 2.0 implementation climate for providers.At the provider level, we will utilize log sheets and interviews to measure the expected tasks to be evaluated, which are (i) screening and recruitment of eligible WLWH, (ii) delivery of HOPE 2.0 to enrolled WLWH, and (iii) follow-up on all testing outcomes and completion of required documentation for these tasks/roles.*Program Effectiveness* is defined as the impact of the ISS on 1) providers' self-efficacy in implementing HOPE 2.0, 2) WLWH screening uptake, and 3) treatment outcome. We will assess effectiveness outcomes at management, provider, and WLWH levels utilizing surveys, log sheets, and interviews.At the management level, we will assess (i) the frequency of support that management delivers to providers, (ii) management self-efficacy in supporting HOPE 2.0 implementation, and (iii) challenges in supporting HOPE 2.0 implementation at their facilities, utilizing log sheets and interviews.At the provider level, we will assess (i) self-efficacy for implementing HOPE, (ii) fidelity of HOPE 2.0 intervention delivery, (iii) number of WLWH screened and women with positive results who are treated, and (iv) the type, frequency, duration, and quality of service provided to patients (WLWH).At the WLWH level, we will assess the impact of HOPE 2.0 on patients’ (WLWH) screening uptake (i.e., service outcome) and receipt of screening results, patient satisfaction, and for women with positive screening results, clinical follow-up, and evaluation for, and receipt of CC treatment where appropriate (i.e., client outcomes). Assessment procedures: WLWH in both study arms will complete the screening and satisfaction outcome survey within one month of completing HOPE 2.0. Within one month of screening, providers will check the lab registry and will review the electronic medical record to confirm screening completion. Treatment compliance will be evaluated within 6 months of positive result notification. The screening and treatment completion outcomes will be binary (yes/no), test results (positive, negative, or inadequate), treatment follow-up (yes, no, or lost-to-follow-up), and patient satisfaction will be measured using a patient satisfaction survey [65].

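### Provider survey scores are compared between arms with no term for staff cadre, although the control arm excepts patient navigator support, so a difference in either direction can arise with no ISS effect

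*Protocol article*

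**What the plan says.** **Who counts as a provider.** Site selection groups "clinicians (doctors, nurses, midwives), and support staff (including patient navigators), collectively referred to as" healthcare providers. The Inclusion criteria require that providers "possess healthcare training and/or qualifications (i.e., patient navigators, physicians, nurses) and work at the HIV clinic". Under Recruitment, the team will "meet with Medical Directors of the selected health facilities to discuss the study and the recruitment of providers", with no restriction by arm. The section on navigator support describes the cadre separately: "Patient navigators, trained lay or volunteer health workers, play a vital role in improving equitable access to, and sustained use of HPVSS".

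**What navigators do in each arm.** In the Intervention arm section, navigators are trained with the other providers. They may hand out kits (Step 3, shared with clinicians) and they support follow-up (Step 4). Control sites follow Steps 2, 3 and 4 as "described in the intervention arm described above, except for patient navigator support".

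**What points the other way.** The Abstract describes the control arm as HOPE 2.0 without ISS. The Design section of the Implementation phase says that control women also receive HOPE. The section on the HOPE intervention lists navigator support as one of its three components.

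**How providers are compared.** The hypothesis is that "implementation outcomes scores among intervention group providers will be significantly higher than those of control group providers". Quantitative data analysis specifies ANOVA between arms for Likert survey items. For continuous outcomes it specifies linear mixed models with an open list of covariates that fit patients, such as insurance and clinical conditions. Staff cadre is not named in either place. Fidelity logs and checklists are aggregated to composite site scores. Penetration is "the proportion of personnel who actually deliver on a HOPE 2.0 program task/role, out of the number trained or expected to deliver" on the particular task or role.

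**The concern.** Navigators are a different cadre from physicians and nurses and do different HOPE work, so their self-efficacy or experience scores could well differ from those of clinicians. If the Control arm exception operates as written, one of two things can follow. Navigators may not be enrolled as control providers, and the two samples then have different staff mixes. Or they may be enrolled with a reduced role or none, and the same cadre is then scored on different work in the two arms.

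Either way, an all-provider ANOVA without cadre mixes any ISS effect with the question of who was surveyed and what they were asked to do. Provider scores are half of the Implementation phase hypothesis, so a difference could be credited to ISS, or a real effect hidden, for this reason alone.

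**Working it through.** **1. Does the plan fix navigators' role in the control arm?** No.
- The exception may remove all navigator activity from control sites.
- It may remove only the follow-up support of Step 4. Navigators could then still hand out kits under Step 3, which control sites must follow.
- The Abstract, the HOPE component list and the Design section imply full HOPE in control, with navigators.

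No section gives the cadre composition of the provider sample in either arm.

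**2. Inputs for the size.**
- From the protocol: 80 providers (Abstract) and two-sided α = 0.05 (Statistical analysis plan section).
- Assumed: equal split, 40 per arm. If only 10 per site respond, as in the baseline survey, there are 20 per arm.
- Assumed: navigator share f, 10–50% in intervention and 0% in control; navigator-minus-clinician score gap d, in within-cadre SD. The protocol gives neither.
- The plan states no provider-level power or effect size, so there is no figure to reproduce.

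**3. Route A: navigators only in the intervention sample, no ISS effect.**

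Spurious difference = (f_int − f_ctl) × d. Two-arm ANOVA (equal to a t-test), 20,000 simulations, no site clustering:

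| f | d | Per arm | Spurious difference (SD) | Rejection rate |
|---|---|---|---|---|
| 10% | 0.5 | 40 | 0.05 | 5.5% |
| 20% | 0.5 | 40 | 0.10 | 7.3% |
| 30% | 0.5 | 40 | 0.15 | 9.4% |
| 30% | 1.0 | 40 | 0.30 | 23% |
| 50% | 1.0 | 40 | 0.50 | 55% |
| 30% | −0.5 | 40 | −0.15 | 9.6% |
| 30% | 1.0 | 20 | 0.30 | 13% |
| 50% | 1.0 | 20 | 0.50 | 29% |

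In the row with d = −0.5, only 0.4% of trials favoured the intervention; nearly all rejections ran against it.

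Hand check of f = 30%, d = 1, 40 per arm:
- Observed variance in the intervention arm ≈ 1 + 0.30 × 0.70 × 40/39 = 1.215; in control, 1. The mean is 1.108, so SD = 1.053.
- Rejection threshold = 1.991 × 1.053 × √(2/40) = 0.469.
- (0.469 − 0.30) / √(2/40) = 0.169/0.2236 = 0.75, an upper-tail probability of about 22.5%. This agrees with the simulation.

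**4. Route B: navigators in both samples, control navigators 1 SD lower for lack of a role.** At 40 per arm the rejection rate is 12% with 20% navigators and 24% with 30%.

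**5. Does attention to cadre remove it?** With 30% navigators in both arms and the same role, the spurious difference is (0.30 − 0.30) × d = 0, and the simulated rate is 3–5%. Under Route B an additive cadre term is not enough: with equal shares the adjusted arm effect is still 0.70 × 0 + 0.30 × 1 = 0.30 SD. The contrast has to be made within cadres that do the same task in both arms.

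**The case against.** **The premise may not hold.** If the exception covers only Step 4 follow-up, or if the statements that control receives HOPE prevail, control navigators keep a role and can be recruited there. A reader might infer that navigators have a HOPE role only in the intervention arm. That is one reading of a single section, and other sections contradict it. The different staff mix is likewise inferred, not documented. This stands, and it is why the passages must be reconciled first.

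**Penetration and fidelity.** A reader might infer that penetration is badly distorted because control navigators would count as staff who fail to deliver. The definition ties the denominator to staff trained for or expected to do the particular task, and Step 2 gives recruitment and message delivery to clinicians. A navigator with no task does not belong in that denominator. Some risk remains only because the definition also admits staff who were merely trained. Fidelity is compared as composite site scores, not as a mean over surveyed individuals. This objection largely stands, so the point is confined to provider survey scores.

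**An unseen analysis plan may add cadre.** The covariate list is open, so it may. But the article does state the survey comparison, as an ANOVA between arms, and that stated comparison is the one at issue.

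**Navigators receive ISS too.** Leaving them out of the contrast narrows what is estimated. This is true and is a real cost of the change.

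**Conclusion.** The point holds in a limited form. On the Control arm section as written, the all-provider ANOVA can compare unlike staff groups, and a difference can appear in either direction with no ISS effect.

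The size cannot be determined from the protocol. With 40 providers per arm, a 0.5 SD gap and 10–30% navigators, the false-positive rate is about 5–9%, which is nominal to mildly raised. It reaches about 23% at 30% navigators and a 1 SD gap, and more only when both share and gap are larger still. All shares, gaps and the equal split are assumptions, and clustering by site is left out.

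The protocol does not support a claim that a false provider effect is likely, that it would favour the intervention, or that penetration and fidelity are affected to the same degree. Whether ISS can be separated from navigator support for the women themselves is a broader question, raised by the same contradiction. Settling it would not by itself say how provider scores are to be compared.

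**What to change.** 1. Reconcile the Control arm exception with the Abstract, the HOPE component list, the Design section and Step 3. State what navigators do at control sites and whether they are enrolled there as providers.
2. In Quantitative data analysis, stratify the provider survey comparison by cadre, or adjust it for cadre (physicians, nurses/midwives, navigators). Name the within-cadre contrast, for cadres with the same HOPE task in both arms, as the one attributed to ISS.
3. Where navigators have no matching control role, report their scores separately as description.
4. Restrict each penetration denominator to staff expected to do that task in that arm.

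**Cost.** Steps 2 to 4 need wording only, since cadre is known at enrolment. Fewer respondents inform the contrast. For illustration, with 30% navigators in an arm of 40, 28 others remain. At equal SD, the standard error rises from √(2/40) = 0.224 to √(1/28 + 1/40) = 0.246 if only the intervention arm loses navigators (about 10% wider). It rises to √(2/28) = 0.267 if both arms do (about 20% wider). Any ISS effect on navigators is then described, not tested.
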